#### 2.3.1. Primary Outcomes 

Psychological Well-Being. The Psychological Well-Being Scales (PWB) [35] will be administered to assess psychological well-being. It is a self-report measure that explores six dimensions: self-acceptance, positive relationships with others, autonomy, environmental control, personal growth, and life purpose. The questionnaire consists of 18 items rated on a 4-point Likert scale ranging from 1 (“completely disagree”) to 4 (“completely agree”). The Italian version [36], assessed for Italian adolescents [37], is reported to have good psychometric properties (test–retest correlation coefficients: Self-acceptance: *r* = 0.82; Positive relationships: *r* = 0.81; Autonomy: *r* = 0.21; Environmental control: *r* = 0.31; Life purpose: *r* = 0.81; Personal growth: *r* = 0.78).

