### 2.8. Sample Size Calculation

In line with previous studies [60,61] to calculate the sample size, an a priori power analysis was carried out using the software G.Power 3.1.9.4 [62]. 

The required sample size was computed for an analysis of variance (ANOVA) with 2 groups (between variable; ACT + TAU vs. TAU) × 2 times (within variable; Time 0/Time 1). To the best of the author’s knowledge, no other similar studies are available in the literature. Therefore, the a priori effect size (Cohen’s *f*) for the global effect (groups x time) was set to 0.2 (small effect size) [63]. Moreover, the Type I error [α] probability was set to 0.05, and the power [1-β] was set to 0.95. In addition, correlation among repeated measures to 0.3 (small–moderate correlation/linear effect). Non-sphericity was assumed, and it was set to 1. Results showed that there is a more than 95% chance of correctly rejecting the null hypothesis of no significant effect of the interaction with an overall sample of 116 subjects: a minimum of 58 participants per group.

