### 2.9. Statistical Analysis 

Descriptive statistical analyses will be conducted to investigate the baseline characteristics of the sample. To evaluate differences between the two groups (ACT + TAU vs. TAU only) across the two time points (pre—Time 0/week 1; post—Time 1/week 3 psychological intervention), repeated measure between groups ANOVAs will be performed for each dependent variable—namely, AFQ-Y, PWB, DASS-21, DERS, and DEBQ. In this case, a global effect size (Cohen’s f and/or eta-squared—η^2^) will be used to quantify the [global] difference of the two groups across times. Global effects size will be interpreted with the following benchmarks [63]: null (*f* < 0.10; η^2^ < 0.003); small (f from 0.10 to 0.25; η^2^ from 0.003 to 0.039); moderate (*f* from 0.25 to 0.40; η^2^ from 0.40 to 0.110); and large (*f* ≥ 0.40; η^2^ > 0.110). Moreover, several focused comparisons will be performed to assess differences both within and between groups. In particular, differences between the two groups will be assessed using an independent samples t-test both at the baseline as well as at the end of psychological treatment, separately—namely, T1: ACT + TAU vs. TAU and T2: ACT + TAU vs. TAU. Conversely, differences within each group across the two time points will be assessed using dependent samples t-test—namely, ACT + TAU: T1 vs. T2; and TAU: T1 vs. T2. The magnitude of the differences will be interpreted by using the Cohen’s d [64]—more in detail, for between-groups comparisons, the classical Cohen’s d formula will be used; in contrast, for within-groups comparisons, the modified formula for dependent data will be used. Each Cohen’s d will be interpreted using the following benchmarks: null (*d* < 0.20), small (d from 0.20 to 0.49), moderate (d from 0.50 to 0.79), and strong (*d* > 0.80). 

Participants who reported missing data as well as subjects who will not participate in each therapy session will be excluded from the final sample, and thus, their data will not be analyzed. Moreover, also, participants who drop out from the program will be excluded from the final sample. 

Analyses will be carried out using Jamovi (version 1.6.15) [64].

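### Section 2.9 does not declare which test decides the trial, and plans ungated within-arm t-tests that cannot show superiority

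*Protocol article*

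**What the plan says.** Section 2.1 describes a parallel-group superiority trial. The abstract and section 2.3.1 name psychological well-being, measured by the PWB, as the primary outcome; the other four scales are secondary.

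Section 2.8 sizes the trial on the group × time term, in terms of "correctly rejecting the null hypothesis of no significant effect of the interaction".

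Section 2.9 then says that "repeated measure between groups ANOVAs will be performed for each dependent variable" and lists AFQ-Y, PWB, DASS-21, DERS and DEBQ together, with no special place for PWB. It continues: "Moreover, several focused comparisons will be performed to assess differences both within and between groups". These comparisons are of two kinds:

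- Between arms: "differences between the two groups will be assessed using an independent samples t-test both at the baseline as well as at the end" of treatment.
- Within arms: "differences within each group across the two time points will be assessed using dependent samples t-test", once in ACT + TAU and once in TAU.

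Each t-test comes with a Cohen's d to be graded from null to strong. Nothing makes the t-tests depend on the interaction result, labels them descriptive, or says which result answers the trial's question.

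**The concern.** A superiority claim needs a comparison between the randomised arms. A paired test inside one arm asks only whether that arm changed. Here both arms receive the three-week inpatient programme with psychological counselling at least weekly (section 2.5), so some change in both is plausible whether or not ACT adds anything.

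When two within-arm p-values stand side by side, it is easy to read significance in one arm and not in the other as an effect of ACT. Grading each within-arm d separately invites the same reading. The error rate of that contrast is not 5%. It depends on how much both arms improve, which nobody controls.

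The other two t-tests raise smaller problems. The post-only comparison is a second answer to the question the interaction already addresses, and the two can disagree. The baseline comparison tests a hypothesis that randomisation makes true.

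**Working it through.** **Inputs from the documents.** Alpha 0.05, power 0.95, f = 0.2, correlation ρ = 0.3, 58 per arm (116 in total), all from section 2.8. The abstract gives 50 participants, about 25 per arm, so both sizes are used below. That conflict is a separate matter.

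**Assumption.** The documents give no expected pre–post change. An equal change of 0 to 0.8 SD in both arms is assumed, with no treatment effect.

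**Step 1: the plan's own figure.** For the interaction, λ = f² × N × m / (1 − ρ), with m = 2 times and 1 and N − 2 degrees of freedom. At N = 116, λ = 0.04 × 116 × 2 / 0.7 = 13.26 and power is 0.951; at N = 114 it is 0.947. The stated 116 reproduces. At N = 50 power is 0.649.

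**Step 2: the within-arm contrast.** In units of the outcome SD, the SD of change is √(2(1 − ρ)) = √1.4 = 1.183. A common change of δ SD gives dz = δ / 1.183. Let p be the noncentral-t power of the two-sided paired test. The arms are independent, so the chance that ACT + TAU improves significantly while TAU is not significant is close to p(1 − p). At δ = 0, where only the improving tail counts, it is 0.025 × 0.95 = 2.4%.

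| Common change (SD) | 58 per arm | 25 per arm |
|---|---|---|
| 0 | 2.4% | 2.4% |
| 0.1 | 8% | 6% |
| 0.2 | 18% | 11% |
| 0.3 | 25% | 18% |
| 0.4 | 20% | 23% |
| 0.5 | 10% | 25% |
| 0.6 | 3% | 22% |
| 0.8 | 0.1% | 9% |

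At the peaks, p = 0.476 (58 per arm, 0.3 SD), so 0.476 × 0.524 = 0.249; and p = 0.527 (25 per arm, 0.5 SD), so 0.527 × 0.473 = 0.249. Since p(1 − p) cannot exceed 0.25, these are ceilings. Simulation with 20,000 replicates agrees: 25.1% at both peaks.

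**Step 3: the between-arm tests.** In the same simulations the interaction test alone rejects in 4.8% to 5.1% of null trials, whatever the common change. If a significant result on either the interaction or the post-only t-test may count, the rate on one outcome is 8.8% to 9.6%.

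**Step 4: the preferred deciding test.** In the step 1 formula, f = 0.2 corresponds to an arm difference in change of 4f = 0.8 SD: (116/4) × 0.8² / 1.4 = 13.26, the same λ. Adjusting Time 1 for Time 0 replaces the variance 2(1 − ρ) = 1.4 by 1 − ρ² = 0.91. Then λ = (116/4) × 0.64 / 0.91 = 20.40 and power is about 99%, against 95% for the interaction. At N = 50, λ = 8.79 and power is about 83%, against 65%.

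**The case against.** The best reply is that a deciding test can be worked out. PWB is named primary, the sample size rests on the interaction, the abstract mentions only the 2 × 2 ANOVAs, and section 2.9 opens with the ANOVA as the analysis of differences between groups. The t-tests come second, as follow-up comparisons. This stands. A reader might infer from section 2.9 alone that the trial has no primary test, but the document read as a whole does not support that. What is missing is a declaration in the section that governs the analysis, where PWB is one of five equal entries and the t-tests are ungated.

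It is also fair that nothing in the article says a conclusion will be drawn from the within-arm results. The route is left open, not chosen, and 25% is a ceiling reached only for particular common changes.

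Finally, only the within-arm tests produce the misleading contrast. The post-only test is a legitimate randomised comparison, and the baseline tests cannot yield an efficacy claim.

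The point still does not reduce to detail that an unseen analysis plan might supply, because the article itself commits to these tests.

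**Conclusion.** The point holds in a limited form. Section 2.9 commits to within-arm tests that cannot answer a superiority question, and does not state that the between-arm PWB comparison decides. If the within-arm contrast were read as an effect, the false-positive chance in favour of ACT would be 2.4% per outcome with no common change and up to 25% at the worst value. It would then fall again, to 0.1% at 0.8 SD with 58 per arm and 9% with 25 per arm. A two-sided 5% test gives about 2.5% in that direction. These figures rest on ρ = 0.3, normal data and an assumed equal change in both arms. Allowing either between-arm test to count gives about 9% on one outcome.

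Two stronger readings are not supported. A reader might take 25% as the trial's error rate, but it applies only at the peak and only if that contrast is used as the verdict. A reader might also infer from section 2.3.1 that each PWB dimension will be tested as primary. That section describes the instrument, and section 2.9 lists PWB as one dependent variable.

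**What to change.** In section 2.9:

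- State that one between-arm comparison of the PWB total score decides. The preferred form is Time 1 adjusted for Time 0. The powered group × time interaction is an acceptable alternative.
- Report within-arm change as a mean with 95% confidence interval and no p-value.
- Delete the baseline t-tests; the planned baseline description is enough.
- Drop the unadjusted post-only t-test, or label it supportive.

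If the adjusted comparison is chosen, add one line to section 2.8 saying that the 116 was calculated for the interaction and is conservative for the adjusted analysis. The cost is wording and fewer p-values to report. No extra participants or measurements are needed.

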## Abstract

This Randomized Controlled Trial [(RCT) aims to evaluate the effectiveness of a brief Acceptance and Commitment Therapy (ACT)-based intervention combined with treatment as usual (TAU) compared to TAU only in improving psychological conditions in a sample of adolescents with obesity (body mass index, BMI > 97th percentile for age and sex) within the context of a wider multidisciplinary rehabilitation program for weight loss. Fifty consecutive adolescents (12–17 years) of both genders with obesity will be recruited among the patients hospitalized in a clinical center for obesity rehabilitation and randomly allocated into two experimental conditions: ACT + TAU vs. TAU only. Both groups will attend a three-week in-hospital multidisciplinary rehabilitation program for weight loss. The ACT + TAU condition comprises a psychological intervention based on ACT combined with a standard psychological assessment and support to the hospitalization. The TAU comprises the standard psychological assessment and support to the hospitalization. At pre- to post-psychological intervention, participants will complete the Avoidance and Fusion Questionnaire for Youth, the Psychological Well-Being Scale, the Depression Anxiety Stress Scale, the Difficulties in Emotion Regulation Scale, and the Emotional Eating subscale of the Dutch Eating Behavior Questionnaire to assess psychological well-being as the primary outcome and experiential avoidance, psychological distress, emotional dysregulation, and emotional eating as secondary outcomes. Repeated-measures ANOVAs (2 × 2) will be conducted. The study will assess the effectiveness of a brief ACT-based intervention for adolescents with obesity in improving their psychological conditions by targeting specific core processes of the ACT framework (openness, awareness, and engagement). Future directions of the study will assess whether these psychological processes will contribute to addressing long-term weight loss.

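### Section 2.9 labels a between-arm Cohen's d below 0.20 'null' from the point estimate alone, a reading the planned sample size cannot support

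*Protocol article*

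**What the plan says.** Section 2.9 plans a 2 × 2 repeated-measures ANOVA for each of five scales, followed by t-tests between and within arms. It then fixes how the size of the results is to be read. For the ANOVA, "Global effects size will be interpreted with the following benchmarks", and the lowest band, called 'null', is f below 0.10 or eta-squared below 0.003. For the t-tests, each Cohen's d "will be interpreted using the following benchmarks: null (*d* < 0.20), small (d from 0.20 to 0.49", then moderate from 0.50 to 0.79 and strong above 0.80.

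The label follows from the point estimate. The article does not make it depend on the ANOVA or t-test result, and mentions no confidence interval or margin.

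The sample size section (2.8) gives "an overall sample of 116 subjects: a minimum of 58 participants per group". The abstract gives "Fifty consecutive adolescents", or about 25 per arm at the 1:1 ratio. That conflict is a separate matter, so both sizes are worked below.

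**The concern.** A magnitude label taken from a point estimate says nothing about how well the magnitude is known. Three of the four labels describe a size. The fourth, 'null', reads as a finding that there is no effect. In a trial declared as superiority (section 2.1) and sized only to detect a difference, a small observed d is usually compatible with a worthwhile effect as well as with none.

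At stake is the wording of the results, scale by scale. A scale on which ACT had a modest benefit could be reported as showing a null effect. A scale on which nothing happened could be reported as showing a small one.

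**Working it through.** **Inputs.** From section 2.8: "the Type I error [α] probability was set to 0.05, and the power [1-β] was set to 0.95"; effect size f "for the global effect (groups x time) was set to 0.2 (small effect size"); "correlation among repeated measures to 0.3"; and "Non-sphericity was assumed, and it was set to 1". Sample sizes are 58 per arm (section 2.8) and 25 per arm (half of the abstract's fifty). The cut-off is 0.20 (section 2.9).

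**1. The plan's own figure.** For the group-by-time interaction, λ = f²·N·m/(1 − ρ) = 0.04 × 116 × 2/0.7 = 13.26 on (1, 114) degrees of freedom. Power is 0.951 at N = 116 and 0.947 at N = 114, so 116 reproduces exactly. In this metric f = 0.2 is a difference in change of 4 × 0.2 = 0.8 SD, that is, a post-treatment d of about 0.8 if the arms start level.

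**2. Interval around a between-arm d.** Near d = 0 the standard error is about √(2/n).
- n = 58: √(2/58) = 0.186, and 1.96 × 0.186 = 0.36.
- n = 25: √(2/25) = 0.283, and 1.96 × 0.283 = 0.55.

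Both exceed 0.20. Inverting the noncentral t distribution gives the same half-widths at d = 0. At 58 per arm it gives −0.18 to 0.55 for an observed 0.19 ('null') and −0.17 to 0.56 for an observed 0.20 ('small'). The two results are almost the same evidence under different labels, and both intervals reach the plan's moderate band. For a 95% interval to fit inside ±0.20 even at an observed d of 0 takes about 194 per arm.

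**3. How often the label misleads.** For a true difference δ, d√(n/2) follows a noncentral t with 2n − 2 degrees of freedom and noncentrality δ√(n/2). The threshold 0.20√(n/2) is 1.08 at n = 58 and 0.71 at n = 25.

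| True d | Event | 58 per arm | 25 per arm |
|---|---|---|---|
| 0 | \|d\| ≥ 0.20, either direction | 28% | 48% |
| 0 | d ≥ 0.20 in favour of ACT | 14% | 24% |
| 0.30 | d < 0.20 | 29% | 36% |
| 0.40 | d < 0.20 | 14% | 24% |
| 0.50 | d < 0.20 | 5% | 14% |
| 0.80 (planned) | d < 0.20 | below 0.1% | 1.7% |

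The 'null' rows take the rule literally, as d < 0.20. Reading it as |d| < 0.20 leaves 29% unchanged at 58 per arm and gives 32% instead of 36% at 25 per arm.

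**4. The f scale.** In the metric of section 2.8, f < 0.10 is a difference in change within ±0.40 SD. The standard error of that difference is √(2(1 − ρ)) × √(2/n). At 58 per arm and ρ = 0.3 it is 1.183 × 0.186 = 0.220, giving half-widths of 0.435 (95%) and 0.364 (90%). With an assumed ρ of 0.62 it is 0.162, and the 95% half-width is 0.32. That value is the mean of the six test–retest coefficients in section 2.3.1 (3.74/6), used here only as an illustration. With no effect, the chance of reaching f = 0.10 on this metric is about 7% at ρ = 0.3 and 1.5% at ρ = 0.62.

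**5. Within-arm d, n = 58.** The 95% half-width is 0.26 when d is scaled by the SD of change. Scaled by the average SD, it is 0.31 at ρ = 0.3 and 0.17 at an assumed ρ of 0.8.

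**The case against.** The strongest reply is that the labels are conventional descriptors and decide nothing. The ANOVAs and t-tests carry the inference. At 58 per arm a between-arm difference is significant only from |d| of about 0.37, so a chance 'small' would normally stand beside a non-significant test. This stands. A reader might infer that noise will be declared a treatment effect, but the article gives no licence for that, because no efficacy conclusion depends on a label.

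A reader might also infer that a trial of this size can never support 'null' on any of the plan's measures. That goes too far. On the f metric of section 2.8 the band is ±0.40 SD of change, and a 90% interval at ρ = 0.3 (0.364) or a 95% interval at ρ = 0.62 (0.32) fits inside it. A within-arm d on the average-SD scale can also fit inside ±0.20 if the pre-post correlation is high. The claim is strict only for the between-arm d.

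Larger error rates can be obtained. If f and eta-squared are computed as partial values from the observed F, chance exceedance of the lowest cut-off is 29% and 56%. The first falls to 7% on the metric of section 2.8. The second comes from an eta-squared cut-off that does not match f = 0.10 (which is 0.01/1.01 = 0.0099), a separate point. Neither is relied on here. Nor is it a complaint that f and eta-squared are unsigned, since the planned comparisons at each time point and within each arm show direction.

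Finally, intervals may be planned in a document not shown. Their absence from the article is therefore not the finding. The finding is the stated rule, and it would need changing even if intervals were added elsewhere.

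**Conclusion.** The point holds for the between-arm Cohen's d. Calling a value below 0.20 'null' is not supportable at 58 per arm, where the 95% half-width is about 0.36, and less so at 25 per arm, where it is about 0.55. The label misleads most when the true effect is absent or modest: 28% of unaffected scales are labelled 'small' or larger, and 29% of scales with a true d of 0.30 are labelled 'null'. Around the planned effect the problem disappears at 58 per arm.

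These figures assume normal scores with equal variance and complete data. Section 2.9 excludes participants with missing data, missed sessions or dropout, so the analysed numbers can only be smaller and the intervals wider. The primary interaction test and its sample size are untouched. This is a fault of interpretation that should be corrected before results are written up.

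**What to change.** In section 2.9:
- For each scale, report the signed between-arm treatment difference, in scale points and in SD units (naming the SD), with its 95% confidence interval, and base the interpretation on that interval.
- Replace 'null' with a neutral term such as 'below small', and state that it is not evidence of no effect.
- Keep f or eta-squared as descriptive statistics.

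A formal rule that claims absence of a relevant effect only when the whole interval lies inside a prespecified range would be sound, but is optional in a superiority trial.

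The cost is a few sentences, with no new data, participants or tests. The downside is that some results will have to be called inconclusive.

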### 2.4. Randomization Procedure

Participants will be randomly assigned to the experimental (ACT+ TAU) or control (TAU) group. We will perform simple randomization with a 1:1 allocation ratio using the web site Randomization.com (http://www.randomization.com) (accessed on 8 June 2021). Randomization will occur after the baseline measurements in order to ensure similar baseline characteristics of groups.

Allocation concealment will be ensured, since all the patients will generate an anonymous code that will be associated with the randomization generated by the program. Researchers will be blind to the association made.

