### 2.5. Procedures 

The trial will be conducted within the context of a three-week in-hospital multidisciplinary rehabilitation program for weight loss based on nutritional, physical, and psychological rehabilitation [50,51,52], according to the Italian National Health System recommendations. As part of the nutritional program, adolescents will be assessed by a staff dietician and placed on an individualized hypocaloric diet composed of 53% carbohydrates, 26% fat, and 21% protein [53] and a fluid intake of at least 1500 mL per day^−1^. They will also follow a daily nutritional counseling program provided both in individual and group settings, comprising dietetics lessons. As for physical rehabilitation, young patients will participate in a physical activity program consisting of five group training sessions per week lasting about 45–60 min per day of physical therapy comprising aerobic activities such as walking and cycling under the supervision of a therapist. The physical program also entails 2 h per week of aerobic leisure activities. As far as the psychological component is concerned, patients will take part in psychological counseling sessions that are provided at least once a week lasting about one hour each, carried out by a clinical psychologist, and aimed at promoting a healthy lifestyle and addressing psychological factors related to the onset of dysfunctional lifestyle habits. 

At week 1 of the hospitalization, all the patients will be screened for admission to the study with a clinical interview conducted by a clinical psychologist blinded to research aims to provide information about the study and assess the eligibility criteria according to the Diagnostic and Statistical Manual of Mental Disorders (DSM-5). Weight and height, to calculate BMI, will be measured by the internal medical team. Once we obtain informed consent to participate from parents and written assent from participants, young patients recruited for the study will be randomly assigned into two conditions. The experimental group will attend TAU plus a brief ACT-based intervention that comprises three sessions, provided once a week, lasting about one hour each, while the control group will attend TAU only. 

At pre (Time 0/week 1) and post-psychological intervention (Time 1/week 3), patients of both conditions will be invited to fill the questionnaires under the supervision of a member of the research team. 

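### The only analysis set described drops randomised patients for missed sessions, missing data or dropout, so the comparison is selected on post-randomisation events, probably more heavily in the ACT arm

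*Protocol article*

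**What the plan says.** Section 2.9 (Statistical Analysis) sets the exclusions: "Participants who reported missing data as well as subjects who will not participate in each therapy session will be excluded from the final sample", with the consequence "and thus, their data will not be analyzed". It adds that "participants who drop out from the program will be excluded from the final sample". The repeated-measures ANOVAs and the t-tests are described for this one final sample. The article names no all-randomised analysis, imputation or sensitivity analysis.

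On timing, section 2.4 states: "Randomization will occur after the baseline measurements in order to ensure similar baseline characteristics of groups". Attendance, dropout and Time 1 completeness are therefore all determined after allocation.

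On the arms, section 2.5 describes an ACT intervention that "comprises three sessions, provided once a week, lasting about one hour each, while the control group will attend TAU only". The same section gives every patient psychological counselling at least weekly during the three-week stay. Section 2.9 does not say whether that counselling counts as a therapy session.

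Section 2.8 asks for 116 patients, "a minimum of 58 participants per group", and mentions no allowance for exclusions.

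**The concern.** Section 2.1 declares a superiority RCT, and the aim is to learn whether adding ACT to TAU helps these adolescents. Randomisation makes the two groups comparable as allocated. It does not make the subgroups who later attend everything, complete every questionnaire and stay to the end comparable.

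The missing-data and dropout clauses are worded alike for both arms. The attendance clause works differently, because the ACT arm has extra sessions and one missed session is enough for removal. If adolescents who attend everything also tend to improve more, the retained ACT group is enriched for improvers to a greater degree than the retained TAU group. A difference could then appear without a treatment effect. If attendance relates to change in the opposite way, a real effect could be hidden. Nothing described in the article would detect or correct either distortion.

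This is a rule that the article fixes. An analysis plan that added an all-randomised analysis would have to contradict it.

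**Working it through.** **1. The plan's own sample size.** Inputs from section 2.8: f = 0.2, two groups, m = 2 times, correlation ρ = 0.3, α = 0.05, non-sphericity 1. For the group × time F test, λ = f²·N·m/(1 − ρ) with 1 and N − 2 degrees of freedom. At N = 116, λ = 0.04 × 116 × 2/0.7 = 13.26 and power is 0.9506. At N = 114 power is 0.9472. The figure of 116 therefore reproduces, and it leaves no margin for losses.

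**2. How unevenly the attendance clause falls.** Assume attendance p per session, independent across sessions and equal in both arms. Three ACT sessions retain p³. Adding about three counselling sessions (at least one a week for three weeks) gives p⁶ in ACT and p³ in TAU.

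| p (assumed) | Only ACT sessions count: ACT / TAU retained | Counselling counts too: ACT / TAU retained |
|---|---|---|
| 0.98 | 94.1% / 100% | 88.6% / 94.1% |
| 0.95 | 85.7% / 100% | 73.5% / 85.7% |
| 0.90 | 72.9% / 100% | 53.1% / 72.9% |

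The filter is heavier in ACT under both readings.

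**3. Bias with no treatment effect.** Let r be the correlation between a normal latent tendency to be retained and the change score, and q the proportion retained. The mean change among those retained is shifted by r·h(q) SDs of change, where h(q) = φ(z_q)/q and z_q is the standard normal quantile at q. One SD of change is √(2(1 − 0.3)) = 1.183 score SDs. Hence

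bias = r × [h(q_ACT) − h(q_TAU)] × 1.183 score SDs.

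Values of h: 0.127 at q = 0.94; 0.350 at 0.80; 0.497 at 0.70; 0.109 at 0.95; 0 at 1. Type I error comes from simulation with 58 per arm and a t-test on change, which is equivalent to the 2 × 2 interaction.

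| Excluded ACT / TAU (assumed) | r (assumed) | Bias, score SD | Type I error |
|---|---|---|---|
| any | 0 | 0 | about 5% |
| 20% / 20% | 0.5 | 0 | about 5% |
| 6% / 0% | 0.3 | 0.3 × 0.127 × 1.183 = 0.05 | about 5.5% |
| 20% / 5% | 0.3 | 0.3 × 0.241 × 1.183 = 0.09 | about 6.4% |
| 20% / 5% | 0.5 | 0.5 × 0.241 × 1.183 = 0.14 | about 9.5% |
| 30% / 5% | 0.5 | 0.5 × 0.388 × 1.183 = 0.23 | about 16% |
| 20% / 5% | −0.3 | −0.09 (against ACT) | not needed here |

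**4. Power net of exclusions, from 116 randomised.** 10% excluded leaves 104 and 92.7%. 20% excluded leaves 92 or 93 and about 89.5%. 30% excluded leaves 81 and 85.2%. To keep 116 analysable, 116/(1 − d) gives 129 at d = 10% and 145 at d = 20%. These figures use section 2.8. The abstract speaks of fifty recruits, a separate conflict that this point does not resolve.

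**The case against.** The strongest reply is that losses may be small. This is a three-week inpatient stay with one ACT session a week, and questionnaires are completed under the research team's supervision. At 98% attendance per session the filter removes about 6% of ACT patients and the distortion is slight. That stands as a comment on size. It is also a reason why analysing everyone would cost little, and section 2.5 lets patients withdraw at any time.

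A reader might infer that TAU patients face no attendance requirement at all, so that motivated ACT completers are compared with nearly every TAU patient. The article does not support this. A therapy session is undefined, all patients receive weekly counselling, and the other two exclusion clauses apply to both arms. What holds is that ACT patients have more sessions to miss.

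A reader might also infer that Time 1 data will not be collected from those who miss sessions. Section 2.5 invites patients of both arms to complete the questionnaires and sets no attendance condition. The fault lies in the analysis set, not in data collection.

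The loss of power is modest, and 58 per group can be read as patients analysed. It would not make this a serious point by itself.

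**Conclusion.** The point holds and needs correction before outcomes are seen. The rule in section 2.9 conditions the only described analysis on post-randomisation events, and its attendance clause probably filters ACT more heavily than TAU under either reading of the term.

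The size is uncertain because the article gives no attendance, dropout or missing-data rates. Under the assumptions shown, the bias runs from zero, through about 0.05 score SD with light exclusion, to about 0.09–0.23 SD with 20–30% against 5% excluded. Type I error runs from about 5% to about 16%. The direction depends on the sign of the correlation between retention and change. It would therefore go too far to say that the rule will produce a false finding in favour of ACT. What can be said is that the planned comparison is open to bias of unknown size and sign. The shortfall from 95% power is secondary.

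**What to change.** Replace the exclusion rule in section 2.9 with a primary analysis of all randomised patients in their allocated arm, whatever their attendance. Use the Time 1 questionnaires already planned for both arms, and state that they are sought from patients who missed sessions too. Handle incomplete data by a method that keeps those patients. A likelihood-based repeated-measures model and multiple imputation are two acceptable choices.

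Keep the full-attendance set only as a labelled supportive analysis, and define which sessions count towards it. In section 2.8, state that the 58 per group are patients analysed, or restate power net of expected losses.

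The cost is protocol wording, modest extra analysis work and possibly a slight dilution of the estimate by non-attenders. Enrolment rises only if the sponsor chooses to protect the 95% power, for example to 129 for 10% losses.
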